### Study design

2.1

This randomized controlled study will be conducted at The Affiliated Hospital of Jiaxing University. Participant recruitment is scheduled to begin on March 2, 2025. A total of 252 female patients undergoing elective surgery will be enrolled and randomly assigned in a 1:1 ratio to either the active rTMS group or the sham rTMS group. Ethical approval for the study was granted by the hospital’s Ethics Committee (Approval No. 2025-KY-049) on February 12, 2025. The trial was registered with the Chinese Clinical Trial Registry on February 14, 2025 (Registration No. ChiCTR2500097991). The schedule for enrollment, interventions, and assessments is presented in Table 1, and study design is illustrated in the flowchart (Figure 1).

**Table 1 tab1:** Study timeline.

Timepoint	Study period					
	On the day pre-operation	on the day of operation	T1	T2	T3	T4
Enrolment						
Inclusion criteria	**×**					
Exclusion criteria	**×**					
Informed consent	**×**					
Randomization	**×**					
Allocation						
Interventions						
Active rTMS group	**×**	**×**				
Sham rTMS group	**×**	**×**				
Outcome measurement						
HADS-A	**×**		**×**	**×**	**×**	**×**
NRS			**×**	**×**	**×**	
POD			**×**	**×**	**×**	
FRAIL			**×**	**×**	**×**	**×**
PSQI			**×**	**×**	**×**	**×**

PSQI, Pittsburgh Sleep Quality Index; NRS, Numeric Rating Scale; POD, postoperative delirium; rTMS, repetitive transcranial magnetic stimulation; FRAIL, Fatigue, Resistance, Ambulation, Illness and Loss of Weight Index; T1, the 1st day post-operation; HADS-A, Hospital Anxiety and Depression Scale-Anxiety subscale; T2, the 2nd day post-operation; T3, the 3rd day post-operation; T4, the 3rd month post-operation.

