### Secondary outcomes

2.7.2

Secondary outcomes comprise: anxiety scores (T1–T4); occurrence of post-operative delirium [evaluated via the Confusion Assessment Technique for the ICU (30) during T1–T3]; pain scores [10-point Numeric Rating Scale (NRS) (31) during T1–T3, 0 = no pain, 10 = worst imaginable pain]; frailty scores [FRAIL Index (32) during T1–T4, 0 = most robust, 5 = most frail]; and sleep quality [Pittsburgh Sleep Quality Index (PSQI) (33) during T1–T4, 0–21, higher scores denote poorer sleep].

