## Sample size

2.10

We conducted a pilot study comparing active versus sham rTMS in female patients. The pilot results showed a mean difference in anxiety scores of 1.3 between groups, with a standard deviation (SD) of 2.9. Depending on a significance level of 0.05 and a power of 0.80, we calculated a sample size of 78 patients/group via PASS 15.0. Accounting for a 10% dropout rate and pre-specified subgroup analyses, we aimed to recruit 126 participants/group to confirm sufficient study reliability.

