## Statistical analysis

2.11

All analyses will be conducted according to the intention-to-treat (ITT) principle, with participants assessed in their originally assigned groups regardless of protocol adherence or treatment received. Baseline demographic and clinical characteristics will be summarized to evaluate balance between the groups. Continuous variables will be assessed for normality using the Shapiro–Wilk test. Normally distributed variables will be presented as mean ± standard deviation (SD) and compared using independent t-tests, while non-normally distributed variables will be expressed as median (interquartile range, IQR) and analyzed using the Mann–Whitney U test. Categorical variables will be expressed as counts and percentages and compared using the chi-square test or Fisher’s exact test.

The primary outcome will be analyzed using a linear mixed-effects model, including treatment group, time, and treatment-by-time interaction as fixed effects, and a random intercept for each subject to account for within-subject correlations. Baseline HADS-A score, age, type of surgery, and relevant perioperative variables (e.g., anesthesia duration) will be included as covariates to control for potential confounding.

Secondary outcomes will be assessed via a linear mixed-effects model, comprising baseline values as covariates. Fixed effects will involve treatment, time, and the treatment-by-time interaction, with a random intercept for subjects accounting for within-subject variability. The treatment-by-time interaction will be initially examined. If significant, group differences and within-group changes at each time point will be assessed, with Bonferroni correction applied for multiple comparisons of baseline changes in anxiety scores. If not significant, only the major effect of treatment will be evaluated, and no Bonferroni correction will be utilized for time-specific treatment effects. Binary outcomes will be compared via the *χ*^2^ test or Fisher’s exact test, with relative risk (RR) and 95% confidence intervals (CI) reported.

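### The correction for visit-by-visit anxiety tests leaves day 3 in the secondary set and is ambiguous when the interaction is not significant; Holm over T1, T2 and T4 would be clearer and somewhat more powerful

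*Protocol article*

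**What the plan says.** The Primary outcome section (2.7.1) makes the HADS-A change from baseline to day 3 (T3) the primary endpoint. The list in 2.7.2 then begins "Secondary outcomes comprise: anxiety scores (T1–T4", so day 3 appears a second time.

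In Statistical analysis (2.11), the paragraph on the primary outcome gives a linear mixed model and states neither a preliminary interaction test nor a multiplicity correction. The paragraph on secondary outcomes uses a similar model with baseline as a covariate and tests the treatment-by-time interaction first.

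- **Interaction significant:** between-group differences and within-group changes are examined at each visit, "with Bonferroni correction applied for multiple comparisons of baseline changes in anxiety scores". The number of comparisons is not given.
- **Interaction not significant:** evaluation is restricted to the main treatment effect, and "no Bonferroni correction will be utilized for time-specific treatment effects".

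**The concern.** Three features of this rule need attention.

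1. **Day 3 sits in two places.** With baseline as a covariate, the day-3 score contrast and the day-3 change contrast estimate the same quantity. The plan can therefore judge it at 0.05 in the primary paragraph and again at a stricter level in the secondary one. Two verdicts on one contrast invite confusion in reporting.
2. **The non-significant branch can be read two ways.** If only the main effect is evaluated, there are no visit-specific effects to correct and the waiver is empty. If the waiver has content, visit-specific effects are reported without correction, and whether they are protected depends on a preliminary test.
3. **Plain Bonferroni spends more power than it needs to.** Holm's step-down procedure controls the same familywise error under any dependence and never rejects less on the same family. Taking day 3 out of the family also leaves fewer tests to correct.

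At stake are the secondary anxiety statements at T1, T2 and month 3.

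**Working it through.** **Inputs.** Sample size (2.10) takes a between-group difference of 1.3 and an SD of 2.9 from a pilot study, with alpha 0.05 and 80% power. It allows for 10% dropout and plans 126 per group. Allocation is 1:1 (2.1). Two-sided testing is assumed, because sidedness is not stated. The correlation between visit contrasts is not in the document; values from 0 to 0.7 were used. SD 2.9 is assumed at every visit.

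**The plan's own figure.** n per group = 2(1.960 + 0.842)² × 2.9² / 1.3² = 78.1, which rounds up to 79, against the stated 78. The one-sided answer is 62, so the two-sided reading fits. Evaluable n = 126 × 0.90 ≈ 113 per group.

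**Power of one between-group contrast at 113 per group.** SE = 2.9 × √(2/113) = 0.386, and 1.3 / 0.386 = 3.37.

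- Level 0.05: Φ(3.37 − 1.960) = 0.92.
- Level 0.05/3 = 0.0167: Φ(3.37 − 2.394) = 0.835.
- Level 0.05/4 = 0.0125: Φ(3.37 − 2.498) = 0.81.

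**Day 3 passing at 0.05 but missing 0.0125.** Before allowing for the interaction test, 0.921 − 0.808 = 0.113, or about 11% of trials. The corrected branch opens only when the interaction is significant, so the share of all trials depends on the effect pattern. At correlation 0.5 it is about 10% if the difference is 1.3 at T1–T3 and zero at T4, 3.5% if the T4 difference is 0.65, and 0.6% if it is 1.3 at all four visits. These figures treat the two day-3 tests as the same statistic. The primary model carries extra covariates, so agreement would be close but not exact.

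**Error under no effect.** Four independent uncorrected tests give 1 − 0.95⁴ = 0.185. For the plan's whole two-branch procedure, four equally correlated z-statistics were simulated (200,000 draws), with a 3-df interaction test at 0.05 and Bonferroni at 0.0125 when it is significant:

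| Correlation | Other branch: main effect only | Other branch: visit tests uncorrected |
|---|---|---|
| 0 | 0.072 | 0.163 |
| 0.5 | 0.058 | 0.140 |
| 0.7 | 0.054 | 0.118 |

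**Gain from Holm over T1, T2 and T4, among trials with a significant interaction** (113 per group, difference 1.3 at T1–T3):

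| Assumed T4 difference | Contrast | Correlation | Bonferroni over T1–T4 | Holm over T1, T2, T4 |
|---|---|---|---|---|
| 0 | T1 or T2 | 0.5–0.7 | about 0.81 | about 0.86 |
| 0.65 | T4 | 0.5 | about 0.07 | about 0.17 |
| 0.65 | T4 | 0.7 | about 0.12 | about 0.27 |

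**Where the gain comes from.** With no T4 effect the interaction is significant in 95% (correlation 0.5) to 99.7% (0.7) of trials, so figures over all trials are nearly the same. At correlation 0.5, T1 power is 0.809 with Bonferroni over four visits, 0.836 with Bonferroni over three, 0.850 with Holm over four and 0.861 with Holm over three. Dropping day 3 and switching to Holm each contribute.

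**The case against.** Bonferroni is a valid choice with simple simultaneous confidence intervals, and at 0.0125 a contrast still has about 0.81 power, roughly the design target. The family size is never stated, and a condensed article may leave it to the analysis plan. All of this stands, and it is why the point is minor.

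Three stronger readings are tempting, and the document does not support them.

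- **That the primary test loses power.** The interaction test and the correction appear only in the secondary-outcomes paragraph. A day-3 result significant at 0.05 as primary keeps that status.
- **That error control is lost when the interaction is not significant.** The sentence containing the waiver first restricts evaluation to the main effect. On that reading overall error is 0.054–0.072. The higher figures apply only if visit-specific effects are nevertheless reported.
- **That each test runs at 0.05/12.** This counts within-group changes in two arms at four visits as well as the four between-group contrasts. The document gives no such number, so no conclusion here uses it.

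Power comparisons that assume 1.3 at all four visits also exaggerate the gain. That pattern has no interaction, so the corrected branch would open in only about 5% of trials. This is why the gains above are conditional on a significant interaction.

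The article does, however, fix a method, a trigger and a waiver, and their wording conflicts. That much is not merely detail left for later.

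**Conclusion.** The point holds as a minor, inexpensive improvement to the secondary anxiety analyses. Day 3's membership of the corrected family is inferred, because it is listed in both outcome sections and nothing in 2.11 excludes it. The waiver in the non-significant branch is ambiguous: harmless on one reading, with overall error of about 0.12–0.14 on the other (correlation 0.7–0.5).

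The power gain is about 5 percentage points at T1 and T2, and 10 to 15 points at month 3 from a low base. It rests on SD 2.9 at all visits, 113 evaluable per group, assumed correlations of 0.5–0.7 and an assumed month-3 difference of 0 or 0.65. The primary conclusion of the trial is not affected.

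**What to change.** Rewrite the two sentences in 2.11 so that:

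1. The day-3 between-group contrast is tested once, as the primary test at 0.05, and is not in the secondary family.
2. The secondary anxiety family is the between-group differences at T1, T2 and T4, tested with Holm's procedure at familywise 0.05.
3. Holm applies whenever visit-specific anxiety effects are reported, whatever the interaction test shows.
4. Within-group changes are descriptive and outside the family.

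No patients or measurements are added. The downside is that Holm has no equally simple simultaneous confidence intervals, so report ordinary 95% intervals beside Holm-adjusted p-values.

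This controls error within the secondary family, not jointly with the primary test. If joint control is wanted, the family can be tested only after day 3 is significant. T1 power is then 0.816 rather than 0.861 (correlation 0.5, no month-3 effect), so most of the gain over Bonferroni's 0.809 is given up.

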### Primary outcome

2.7.1

The primary outcome is the change in anxiety score from baseline to 3 days post-operation, measured using the HADS-A (25), with a score of ≥8 indicating clinically significant anxiety (26). The minimal clinically important difference (MCID) for the Hospital Anxiety and Depression Scale (HADS) is not fixed and varies across clinical contexts and analytical methods. Evidence from anchor-based studies and systematic reviews suggests that a change of approximately 1.5–2.0 points in the HADS total or subscale scores is generally considered clinically meaningful (27–29). Anxiety was assessed preoperatively in the ward on the day pre-operation (T0) prior to the first rTMS intervention, and the second intervention was administered in the pre-operative holding area on the day of operation. Postoperative anxiety scores were measured on days 1 (T1), 2 (T2), 3 (T3), and the 3rd month post-operation (T4).

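### The day-3 primary outcome has no named test, and the only stated testing rule conditions time-point comparisons on a significant treatment-by-time interaction

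*Protocol article*

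**What the plan says.** Section 2.7.1 (Primary outcome) fixes one time point: "The primary outcome is the change in anxiety score from baseline to 3 days post-operation", measured with HADS-A. HADS-A is collected at T0 and at four later times: days 1, 2 and 3 (T1-T3) and month 3 (T4). Section 2.7.2 lists anxiety at T1-T4 again as a secondary outcome.

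Section 2.11 (Statistical analysis) gives the primary model: "The primary outcome will be analyzed using a linear mixed-effects model, including treatment group, time, and treatment-by-time interaction as fixed effects", with a random intercept. Baseline is a covariate: "Baseline HADS-A score, age, type of surgery, and relevant perioperative variables" are adjusted for. No coefficient or contrast is named as the primary test.

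The next paragraph opens "Secondary outcomes will be assessed via a linear mixed-effects model, comprising baseline values as covariates" and contains the section's only testing rule. The interaction is examined first. If it is significant, groups are compared at each time point, "with Bonferroni correction applied for multiple comparisons of baseline changes in anxiety scores". If it is not: "If not significant, only the major effect of treatment will be evaluated, and no Bonferroni correction will be utilized for time-specific treatment effects".

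Section 2.10 (Sample size) uses a difference of 1.3, SD 2.9, significance level 0.05 and power 0.80. It gives 78 per group, raised to 126 for 10% dropout and subgroup analyses.

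**The concern.** A model with treatment, time and their interaction offers several candidate tests of treatment: the interaction, the main effect, and a contrast at each time. The primary outcome calls for one of these, the contrast at day 3, and the text does not say so.

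The one rule it does state suits a day-3 question badly. A benefit that is equally large at every visit produces no interaction, so the rule sends that trial to a main effect averaged over T1-T4, month 3 included, and away from day 3. Where the interaction is significant, day 3 is tested with a Bonferroni penalty that the sample size did not allow for.

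The sentence for a non-significant interaction is also inconsistent. It restricts the analysis to the main effect, then says that time-specific effects need no correction, as if they were still to be tested. What counts as primary success would therefore be open to choice after the data are seen.

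**Working it through.** **Inputs.** Difference 1.3, SD 2.9, alpha 0.05 (two-sided assumed), power 0.80, 126 per group and 10% dropout are from section 2.10. Evaluable per arm: 126 × 0.9 = 113.4, taken as 113. The four response times T1-T4 follow from section 2.7.1, with baseline as a covariate (section 2.11). The within-subject correlation ρ is not given, so 0.3, 0.5 and 0.7 are assumed, with equal SD and correlation across times.

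**The plan's own figure.** n = 2 × (1.960 + 0.842)² × (2.9/1.3)² = 78.1 per group. That rounds up to 79 (80 with the t distribution), against 78 stated. The figure is reproduced to within two patients. It is a plain comparison of two means, with no gate and no Bonferroni step.

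**Direct day-3 contrast, 113 per arm.** SE = 2.9 × √(2/113) = 0.386, and 1.3/0.386 = 3.37. Power = Φ(3.37 − 1.96) = 92.1%. With 126 per arm it is 94.5%. Bonferroni over four times moves the critical value to 2.498, and power at 113 per arm falls to Φ(3.37 − 2.498) = 80.8%, before any gate.

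**The gate.** The interaction test on 3 degrees of freedom has noncentrality λ = Σ(δₜ − mean δ)² / [2 × 2.9² × (1 − ρ)/113].

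- *Constant benefit (1.3 at T1-T4).* All deviations are zero, so λ = 0 and the gate opens at its own alpha, about 5%, whatever ρ is.
- *Benefit at T1-T3, none at T4.* The mean is 0.975 and the sum of squares is 3 × 0.325² + 0.975² = 1.2675. With ρ = 0.5, λ = 1.2675/0.0744 = 17.0 and the gate opens in about 95% of trials.

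**The whole rule, simulated** (40,000 runs per case, 113 per arm, Bonferroni over four times):

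| Scenario | ρ | Gate opens | Day 3 tested and significant | Direct day-3 contrast |
|---|---|---|---|---|
| 1.3 at T1-T4 | 0.3 | 5.2% | 3.6% | 92.1% |
| | 0.5 | 5.1% | 3.7% | 92.2% |
| | 0.7 | 5.2% | 3.9% | 92.1% |
| 1.3 at T1-T3, 0 at T4 | 0.3 | 84.6% | 69.6% | 92.1% |
| | 0.5 | 94.9% | 77.2% | 92.2% |
| | 0.7 | 99.7% | 80.7% | 92.1% |

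**The averaged main effect.** Under a constant benefit its power is 97.0-99.9%. The rule reaches it by the non-significant branch, and finds it significant there, in 92-95% of all trials.

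It is nevertheless a different quantity from the day-3 effect. With 1.3 at T1 and T2 and nothing at day 3 or month 3, the average is 0.65. If the main effect were simply adopted as the primary test, it would be significant in 48-69% of trials with no day-3 benefit. Under the literal rule this would seldom happen, because the interaction would be significant in 94-100% of those trials.

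**The case against.** The strongest reply is that the primary outcome has its own paragraph, with its own model and no gate. The rule comes under secondary outcomes, where anxiety at T1-T4 is also listed, so its reference to anxiety has a natural secondary meaning. On that reading the 5% figure does not touch the primary test, and the exact contrast could be left to an SAP. This stands as far as it goes: applying the rule to the primary outcome is an inference. But the day-3 score is then both primary and secondary, no other rule exists, and the text does not say which applies. The self-contradicting sentence is a defect on either reading.

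The 5% also depends on baseline not being a response level. If T0 were one, a constant post-operative benefit would open the gate in 84-99.8% of trials at 113 per arm. Baseline as a covariate points the other way, but the rule also mentions within-group changes.

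A reader might infer more than the documents support:

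- *That a constant benefit would be missed.* It would not be. The main effect would usually find it, and in that scenario the average equals the day-3 effect.
- *That false positives are seriously inflated.* Four uncorrected time-point tests would give 13-18%, but the rule as written limits the second branch to the main effect. Followed literally, it rejects something under the null in about 5-6% of trials for ρ of 0.3-0.7.
- *That the random intercept makes the day-3 test anti-conservative.* That needs SDs which differ over time in a particular direction. The plan gives one SD, 2.9, and equal SDs leave alpha at 0.05. Unstructured covariance is a preference here.
- *That the within-group comparisons are an efficacy claim.* The plan nowhere uses them as one.

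**Conclusion.** The point holds as a badly stated primary test. The outcome is fixed at day 3, the model paragraph does not tie the test to day 3, and the only rule given is ambiguous in scope, unsuited to a day-3 question and internally inconsistent.

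Its size is conditional. If the rule governs the primary outcome and baseline is a covariate, a constant 1.3-point benefit reaches a day-3 test in about 5% of trials. With benefit at T1-T3 only, gated day-3 power is about 70-81%, against 92% for the direct contrast with 113 per arm. These figures assume SD 2.9 at every time and ρ between 0.3 and 0.7. If the rule is meant for secondary outcomes only, they do not apply to the primary test; the remaining defects are an unnamed primary contrast and day-3 anxiety data that fall under two testing regimes.

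On either reading, the sample size matches a single two-group comparison at 0.05. Neither the gated test nor the averaged effect is the one that was powered.

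**What to change.** In section 2.11:

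1. State that the primary test is the baseline-adjusted between-group difference in HADS-A change from T0 to T3, estimated from the mixed model, at two-sided alpha 0.05, performed whatever the interaction shows and without Bonferroni.
2. State that the interaction rule applies only to secondary outcomes and to the other anxiety time points (T1, T2 and T4).
3. Rewrite the sentence on a non-significant interaction so that it says either that time-specific effects are not tested, or that they are, and with what correction.

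This changes wording only. It needs no further patients, visits or data, and the existing sample size already fits the single day-3 comparison. It should be settled before treatment codes are broken.

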## Study interventions

2.5

All rTMS procedures were performed by professionally trained and experienced operators who had undergone standardized training prior to study initiation. The rTMS intervention is administered on the day before surgery and the day of surgery, resulting in two sessions per participant. This protocol is designed to accommodate the limited perioperative time window while providing a rapid, clinically feasible intervention.

Stimulation parameters are based on established neurophysiological principles. The right dorsolateral prefrontal cortex (DLPFC) is selected as the target region due to its role in negative emotional processing and its involvement in anxiety-related neural circuits. Low-frequency (1 Hz) stimulation is applied to reduce cortical excitability and modulate prefrontal–limbic pathways. The entire procedure strictly followed a unified protocol to ensure consistency in coil positioning, stimulation parameters, and patient interaction.

First, a circular coil was used to locate the stimulation target. The primary motor cortex (M1) was clinically identified as the area 2 cm anterior and 1–1.5 cm lateral to the intersection of the naso-occipital line and the temporoparietal line on the patient’s scalp (i.e., the Cz point). The resting motor threshold (RMT) for each patient was then determined as a reference for setting the stimulation intensity, expressed as a percentage of the rTMS device’s maximum output (24). The RMT was defined, using the visual observation technique, as the lowest stimulation intensity capable of eliciting a visible contraction in the target muscle in 5 out of 10 trials while the muscle was completely relaxed (24). Subsequently, a figure-8 coil was used to target the right DLPFC. The center of the coil was positioned parallel to the patient’s scalp, with its midpoint aligned directly over the stimulation site. The rTMS treatment was then delivered at an intensity of 80–120% of the RMT using a low frequency of 1 Hz (21). Both groups will undergo the intervention using identical devices and operational procedures. However, in the sham rTMS group, the device will not deliver pulsed magnetic fields to the brain but will only produce similar audible clicking sounds and scalp sensations/vibrations mimicking those emitted during active stimulation.

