In the exploratory analyses, to investigate the heterogeneity of rTMS effects across subgroups within the anxious population, we performed a series of subgroup analyses for the primary outcome measure. The primary subgroup analysis was depending on the level of patient anxiety: individuals with a HADS-A score ≥8 were defined as having anxiety symptoms, with scores of 8–10 (mild), 11–14 (moderate), and 15–21 (severe). We also examined subgroup effects according to surgery type, PSQI score (≤15 vs. > 15), and FRAIL scale result (no frailty vs. pre-frailty or frailty). These analyses were conducted by adding an interaction term between the treatment group and the subgroup variable to the linear mixed-effects model for the primary outcome. Effect heterogeneity was examined by estimating the importance of interaction terms. The adjusted odds ratio (aOR) and its 95% CI for each subgroup were displayed in a forest plot.

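### No pre-treatment PSQI, FRAIL or NRS is scheduled, yet section 2.11 adjusts for baseline values of the secondary outcomes and defines subgroups by PSQI and FRAIL

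*Protocol article*

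**What the plan says.** **Timing of treatment.** Section 2.5: "The rTMS intervention is administered on the day before surgery and the day of surgery". Table 1 defines the first postoperative assessment as "T1, the 1st day post-operation", so everything from T1 onwards follows both sessions and surgery.

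**Timing of measurement.** Section 2.7.1 describes one pre-treatment assessment: "Anxiety was assessed preoperatively in the ward on the day pre-operation (T0) prior to the first rTMS intervention". Section 2.7.2 gives the windows for the other scales: "pain scores [10-point Numeric Rating Scale (NRS) (31) during T1–T3", "frailty scores [FRAIL Index (32) during T1–T4" and "sleep quality [Pittsburgh Sleep Quality Index (PSQI) (33) during T1–T4". Table 1 agrees: in its outcome block only HADS-A is marked on the day before surgery, and the NRS, FRAIL and PSQI rows begin at T1.

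**Analysis.** Section 2.11: "Secondary outcomes will be assessed via a linear mixed-effects model, comprising baseline values as covariates". Its exploratory part adds: "We also examined subgroup effects according to surgery type, PSQI score", with PSQI cut at ≤15 versus >15, and also FRAIL status (not frail versus pre-frail or frail). Each enters as a treatment-by-subgroup interaction in the primary-outcome model. No measurement time is given for either subgroup variable.

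**The concern.** The analysis section calls for data that the schedule does not collect. There are two separate consequences.

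1. **Covariate.** A baseline value of PSQI, FRAIL or NRS cannot enter a model if none is taken. The randomised comparison stays unbiased without it, but the precision and the correction for chance imbalance that the plan promises are lost for these outcomes.
2. **Subgroups.** The only scheduled PSQI and FRAIL scores that could define the strata are post-treatment scores, which the trial also tests as secondary outcomes. If rTMS shifts them, active and sham patients in the same stratum are no longer comparable. The within-stratum effect is then biased, and the interaction test can show heterogeneity where there is none.

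The subgroups also bear on recruitment, because section 2.10 cites pre-specified subgroup analyses among its reasons for recruiting 126 per group.

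**Working it through.** **Step 1. Schedule against analysis**

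| Scale | Pre-treatment (T0) value scheduled | First scheduled value | Baseline covariate implied in 2.11 | Subgroup variable in 2.11 |
|---|---|---|---|---|
| HADS-A | yes | T0 | yes, available | yes, available |
| PSQI | no | T1 | yes, not available | yes, no T0 value |
| FRAIL | no | T1 | yes, not available | yes, no T0 value |
| NRS | no | T1 | yes, not available | no |
| Delirium | no | T1 | no (χ² or Fisher test) | no |

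Table 1 and section 2.7.2 state the windows separately and agree, so a badly extracted table does not explain the gap.

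**Step 2. The plan's own sample size**

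Inputs from section 2.10: difference 1.3, SD 2.9, alpha 0.05, power 0.80. Two-sided normal approximation:

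n = 2 × (1.960 + 0.842)² × 2.9² / 1.3² ≈ 2 × 7.85 × 8.41 / 1.69 ≈ 78.1 per group.

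The stated 78 is reproduced to within rounding (79 when rounded up, 80 by the t-test version). Allowing for 10% dropout gives 78 / 0.9 = 86.7, so 87. The remaining 126 − 87 = 39 per group are attributed to the subgroup analyses, two of which have no scheduled pre-treatment variable.

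**Step 3. Size of the subgroup bias**

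From the protocol: HADS-A effect 1.3, SD S = 2.9, cut at 15. Assumed, because the protocol gives no PSQI figures: postoperative PSQI normal with SD 4, sham mean m from 10 to 15, rTMS lowering PSQI by d = 1 to 2 points, within-arm correlation r between PSQI and HADS-A of 0.3 to 0.5, and a true HADS-A effect that is the same for everyone.

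Let a₀ = (15 − m)/4 for sham and a₁ = (15 − m + d)/4 for active. With φ and Φ the standard normal density and distribution function, let λ(a) = φ(a)/Φ(a) and κ(a) = φ(a)/(1 − Φ(a)). The apparent benefits are:

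- PSQI ≤15: 1.3 − r·S·[λ(a₀) − λ(a₁)]
- PSQI >15: 1.3 − r·S·[κ(a₁) − κ(a₀)]

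Example with m = 10, d = 2, r = 0.5: a₀ = 1.25, a₁ = 1.75, r·S = 1.45.

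- ≤15: 1.3 − 1.45 × (0.2042 − 0.0899) = 1.13
- >15: 1.3 − 1.45 × (2.1537 − 1.7288) = 0.68
- Spurious gap: 0.45

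The two ends of the assumed range:

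| Sham PSQI mean | d = 1, r = 0.3: ≤15 / >15 (gap) | d = 2, r = 0.5: ≤15 / >15 (gap) |
|---|---|---|
| 10 | 1.24 / 1.12 (0.13) | 1.13 / 0.68 (0.45) |
| 12 | 1.21 / 1.13 (0.08) | 1.03 / 0.72 (0.31) |
| 14 | 1.18 / 1.15 (0.04) | 0.93 / 0.77 (0.16) |
| 15 | 1.17 / 1.16 (0.01) | 0.88 / 0.80 (0.08) |

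With d = 0, a₀ = a₁ and both strata return 1.3: no bias. The mechanism is the same for FRAIL, but no figure was computed for it.

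**Step 4. Bias against noise**

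In the example, 126 × 0.106 ≈ 13.3 sham and 126 × 0.040 ≈ 5.0 active patients exceed 15, leaving about 112.7 and 121.0 at or below it. Taking SD 2.9 in every cell, the standard error of the gap is about 2.9 × √(1/13.3 + 1/5.0 + 1/112.7 + 1/121.0) ≈ 1.6 points. The largest bias in the table is well below that.

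**The case against.** **The windows may list outcome times only.** Section 2.11 also promises a summary of baseline demographic and clinical characteristics without itemising them, and a condensed article may leave that list to the full protocol. This stands in part. A reader might infer that these scales are certainly never taken before treatment, or that the plan states it will stratify on post-treatment scores. The document says neither; it gives no time point for the subgroup variables. What it supports is that no pre-treatment measurement is scheduled, in two places that agree, while the analysis needs one.

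**The affected analyses are secondary or exploratory.** This also stands. A reader might infer that the trial's main result is at risk. It is not: HADS-A has a T0 value, so the primary model, the anxiety-severity subgroups and the HADS-A secondary analyses are sound. The surgery-type subgroup and delirium need no baseline score. Leaving out the covariate does not bias the NRS, FRAIL or PSQI comparisons. Against this, section 2.10 uses subgroup analyses to support the larger sample.

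**The bias may be trivial.** It depends wholly on whether rTMS changes the stratifying score. A reader might also infer that stratum effects could be roughly halved. With the same formulas, a gap of 0.56 (1.22 against 0.66) needs a sham PSQI mean of about 8, where only about 5 sham and 1–2 active patients of 126 each would exceed 15. Nothing in the documents supports that as the expected case. Still, PSQI and FRAIL are tested as outcomes, so the plan cannot assume that rTMS leaves them unchanged.

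**Conclusion.** The inconsistency is real and should be fixed, but its reach is limited to secondary and exploratory analyses. As scheduled, baseline adjustment is not possible for PSQI, FRAIL and NRS, and the PSQI and FRAIL subgroups have no pre-treatment variable to rest on. For NRS the problem is only the covariate sentence, since it defines no subgroup.

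The covariate problem costs precision, not validity. The subgroup problem is one of validity, conditional on rTMS affecting PSQI or FRAIL. The ranges shown rest on the assumed PSQI mean, SD, treatment effect and correlation, on normality, and on a simple difference between arms in place of the planned mixed model. They indicate direction and rough size and do not forecast this trial's results.

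**What to change.** 1. **Table 1 and section 2.7.2:** add PSQI and FRAIL on the day before surgery (T0), completed with HADS-A before the first rTMS session.
2. **Section 2.11, secondary outcomes:** use the T0 values as covariates for PSQI and FRAIL, and limit the baseline-adjustment sentence to outcomes that have a T0 value. That resolves NRS without a new measurement.
3. **Section 2.11, subgroups:** state that the PSQI and FRAIL subgroups are defined by T0 values only.
4. **Participants already enrolled without T0 values** (recruitment was due to start in March 2025): leave them out of the PSQI and FRAIL subgroup analyses and do not claim baseline adjustment of those outcomes for them. If T0 values cannot be collected at all, drop both subgroups.
5. If T0 values of these scales are in fact already collected, correcting the schedule and stating the subgroup time point is enough.

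The cost is two short questionnaires at a visit that already takes place, an amended table and a few sentences, with no additional patients. Pre-treatment values that were not taken cannot be recovered later, so the change is worth making promptly.
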